### Trial design {8}

The presented trial is a parallel-group, two-arm superiority RCT to evaluate the efficacy of a peer-supported IMS intervention for patients with type 2 diabetes mellitus in Lower Austria. Peer support via IMS in addition to standard therapy is compared with stand-alone standard therapy.

Moderators play a central role in peer-supported IMS intervention because they initiate and moderate the IMS exchange and discussion. They are patients with several years of disease and therapy experience because they need personal and practical experience in order to provide supportive and credible coaching. All moderators receive prior training and guiding material (see {11a}). The moderators are supported by a dietitian at regular intervals and by other study team members if needed. One moderator is responsible for one IMS group consisting of 14 participants maximum.

The participants will be fully informed about all aspects of the trial and asked to sign a consent form. The participants will be randomized at a ratio of 1:1.

The duration of the intervention is 7 months, followed by a 7-month follow-up period. The intervention will be performed twice to expand the recruitment phase. During the follow-up, the intervention group is expected to use the IMS tool without guidance by health professionals and both groups receive standard therapy.

## Methods: participants, interventions, and outcomes

### Study setting {9}

The trial will be implemented in Lower Austria, which is a federal state in northeastern Austria. It is the country’s largest federal state and surrounds the Austrian capital Vienna. Lower Austria had 1,684,287 residents in 2020 [46], which reflects approximately 19% of all inhabitants of Austria [47].

Lower Austria has the second-highest prevalence of diabetes among all Austrian federal states. In this region, 5.7% of all residents above the age of 14 are affected by diabetes [3].

The trainings and medical examinations will be carried out at the St. Pölten University of Applied Sciences (located at the center of Lower Austria) and the hospitals in Wiener Neustadt (in the southeast of Lower Austria), Hollabrunn (in the northwest of Lower Austria) and Mauer/Amstetten (in the southwest of Lower Austria). This equal distribution throughout Lower Austria guarantees easy trial access for all participants. Biochemical analysis will be carried out at the University Hospital St. Pölten (located at the center of Lower Austria).

### Eligibility criteria {10}

Participants eligible for the trial must meet all of the following criteria during randomization:

#### Inclusion criteria participants (excluding moderators):

Older than 40 yearsLiving in Lower AustriaDiagnosed with type 2 diabetes mellitus according to the Austrian definition [4]HbA_1c_ of ≥ 6.5% (48 mmol/mol) in the most recent measurementUndergoing standard therapy [4]Have been receiving oral hyperglycemic agents for a maximum of 3 years prior to the start of the trial (first prescription of a minimum of two packages per year to exclude wrong prescriptions)

#### Inclusion criteria moderators:

The inclusion criteria for moderators differ from the inclusion criteria for other participants because moderators are required to be more experienced in the management of their disease in order to be able to authentically share personal and practical experiences and to effectively support participants.

Therefore, they should (1) be interested, (2) be engaged in therapy participation and judged by the practice team as being generally adherent to therapy, (3) have the capacity and commitment to undergo the training, (4) have a complete understanding of the importance of data security and patients’ confidentiality, (5) cooperate with the dietitian and the study team if problems arise, (6) have the ability to fully understand the IMS strategy and the possibilities within the IMS tool, and (7) have several years of diseases experience (no newly diagnosed patients).

Therefore, their inclusion criteria are:
Older than 60 yearsLiving in the vicinity of the training location in St. Pölten, which means residing in St. Pölten, St. Pölten Land, Melk, Krems, or LilienfeldDiagnosed with type 2 diabetes mellitus according to the Austrian definition [4]HbA_1c_ of ≥ 6.5% (48 mmol/mol) in the most recent measurementUndergoing antidiabetic therapy according to the current guidelines [4]Have been receiving oral hyperglycemic agents for a minimum of 3 years prior to the start of the trial (first prescription of a minimum of two packages per year to exclude wrong prescriptions)Engaged participation (regular participation) in the Austrian disease management program “Therapie aktiv – Diabetes im Griff,” which is provided by the Austrian Health Insurance Fund

#### Exclusion criteria for participants as well as moderators:

Insulin dependencyHospitalization or vacation of more than 3 weeks during the interventionEye disorders that severely limit vision and, hence, inability to read the display (e.g., proliferative retinopathy or macular edema)Severe illnesses such as kidney, liver, heart disease, malignant cancer, or neurological or mental illness which make a longer hospitalization likelyIllicit drug use or non-medical use of prescription drugs determined by a single-question screening test for drug use and drug use disorders in primary care [48]Limited German language skills determined during the initial appointment concerning the informed consentPregnancy

### Who will take informed consent? {26a}

Interested participants can register using an online registration form and a central study staff member - a dietitian or a nutritionist - will contact them afterwards.

During the initial appointment, which will be conducted online via MS Teams or face to face at the St. Pölten University of Applied Sciences, the staff member will explain the trial (background, protocol, different roles, importance of randomization and adherence) to potential participants and will review the consent form. Furthermore, the staff member will answer any questions arising. When the trial and its requirements are understood completely, the informed consent form will be signed by the participant. This can be done via electronic or handwritten signature.

All eligible participants must complete the consent procedure before enrolment and randomization. There are separate consent forms for general participants and for moderators.

#### Compensation

Participants and moderators will get a financial compensation in the amount of 50 EUR and a small gift after the last measurement. Furthermore, the results of the Bioelectrical Impedance Analysis measurements (BIA) in the context of body weight, body height, waist circumference, and blood pressure can be discussed with a dietitian for free after each measurement.

### Additional consent provisions for collection and use of participant data and biological specimens {26b}

No ancillary study will be conducted.

## Interventions

### Explanation for the choice of comparators {6b}

For the intervention group, we will use the instant messaging tool *mattermost* as android/iOS and web/desktop application, in addition to standard therapy. *mattermost* is an instant messaging service application that is installed on the cell phone and works similar to WhatsApp, i.e., people can use *mattermost* to send each other messages, photos, etc. Unlike WhatsApp, the messenger allows to track conversations and metadata of the participants, but *mattermost* is hosted in an ISO-certificated data center in Vienna for the duration of the project. Thus, it is hosted according to the European General Data Protection Regulation. The *mattermost* Starter Version (self-managed) is available for free, but the setup and secure hosting as well as the secure data extraction implementation is chargeable. For our participants, it has the look and feel of frequently used messenger tools, e.g., WhatsApp.

### Intervention description {11a}

The intervention is developed and conducted by an interdisciplinary team. Dietitians and moderators play an active role in the operational process of the intervention.

Dietitians are part of the team that develops the training curricula and is responsible for the training of the moderators and participants. They will supervise all moderators once a month via online meetings. During these meetings, the dietitians support moderators, e.g., if specific knowledge concerning diabetes care is needed or in case of technical problems.

Moderators act as facilitators and coordinators but they do not give medical or disease-related advice. In order to moderate communication and exchange in the IMS group effectively and authentically, personal and practical disease-related experiences of the moderator and the readiness to share these experiences with the group are essential. Moderators receive 9 h of training on the content to be shared via IMS and communication strategies to facilitate group exchange, peer support and behavioral change.

Participation in the clinical trial will last 15 months (1 month training/first measurement, 7 months intervention, 7 months follow-up). 196 participants will be randomly assigned to one of two groups: the intervention group or the control group. Participants who are randomly assigned to the intervention group will attend a 2 h technical training in connection with the first measurement. In the course of this training, they will learn how to use the *mattermost* app. After this training, they will join a *mattermost* group (instant messaging service group) with a maximum of 14 people for 14 months (7 months guided and seven without guidance). For the first 7 months of the intervention, an empowerment-based IMS communication strategy for diabetes self-management peer support has been developed.

Moderators are provided with a detailed handbook on web-based diabetes-related content and communication strategies to share this content with the group.

The IMS strategy combines two aspects that are essential for IMS diabetes self-management peer support: 1. a communication strategy that takes into account the special requirement of IMS communication, i.e., approaches to raise engagement and activities in the group, and 2. a diabetes self-management support strategy to make sure that all topics which are known to be of importance for diabetes self-management [49] are covered and shared in a way that enables and empowers participants in their disease management. Thus, the IMS communication strategy contains, on the one hand**,** the IMS strategy which also involves a communication strategy that considers the special requirements of IMS and peer-communication on how to react and act in certain situations, for example, to achieve engagement. On the other hand, it entails a didactic plan which outlines how, in what form and how frequently diabetic content shall be shared with the participants by moderators (e.g., web links, exchange of personal experiences/opinions). This IMS strategy will be operationalized in form of the training curriculum.

The moderator and the way she or he communicates with the group plays a vital role in guiding the group, setting the tone and creating an atmosphere of trust and providing support. By introducing the moderators to certain communication strategies that are also displayed in detail in the guidebook and can be reflected upon in the monthly meeting with the dietitian, a trusting atmosphere in the IMS group should be facilitated.

After the intervention, a 7 month follow-up will be conducted. During the follow-up, the intervention group may use the IMS tool in a self-organized manner, i.e., without guidance by the dietitian, and continue to receive their standard therapy.

Participants who are assigned to the control group will continue to receive their standard therapy but will not be assigned to a *mattermost* group.

The intervention will be conducted twice to increase the recruitment phase. The first intervention will start in April 2022. As soon as the first cohort enters the unaccompanied phase, a second moderated cohort will start - in both cases accompanied by an equally large control group. In total, we will be in the field for 23 months. With the start of the first intervention, we will have as many intervention and control teams with 14 people each as there are registrations. With the second intervention date, the remaining persons (196 in total) form further intervention and control teams.

### Criteria for discontinuing or modifying allocated interventions {11b}

Participants can revoke their willingness to participate at any time, even without giving reasons, and withdraw from the clinical study without this causing them any disadvantages for their further medical care.

The principal investigator may terminate a participation in the study prematurely without obtaining the participant’s consent beforehand. The reasons for this may be:
Participants do not longer meet the inclusion requirements of the clinical trialThe treating doctor reasons that continued participation in the clinical trial is not in the participant’s best interestThe study coordinator makes the decision to terminate the entire clinical trial, or to terminate only one subject’s participation prematurely

The communication protocols (see also {12}) based on activities within the IMS tool *mattermost* are reviewed weekly. The results of these reviews are used-in addition to the planned analysis of the KPIs-to monitor the intervention group and to intervene if necessary. Thus, they help the study coordinator and selected study team members to stay informed and, in case of extraordinary events (e.g., mobbing), to decide whether to continue, modify, or prematurely terminate the work with certain participants, moderators, or communication concepts. If a participant does not adhere to the communication rules (netiquette) previously agreed upon in each IMS group, even after several discussions, he or she will be excluded.

### Strategies to improve adherence to interventions {11c}

The intervention consists of a peer-supported IMS intervention in addition to standard therapy. Therefore, adherence of participants to the IMS intervention pertains mainly to the IMS strategy, the measurements, and the initial training sessions.

The first step to improve adherence is the holistic explanation of the trial to interested participants during the initial appointment [50, 51]. In this appointment, sufficient time is scheduled in order to enable comprehensive understanding concerning the trial among participants.

Those who have greater responsibility - the moderators - will be individuals participating in the disease management program “Therapie aktiv – Diabetes im Griff” (https://www.therapie-aktiv.at), which is provided by the Austrian Health Insurance Fund. Hence, they are already proven to be generally adherent and engaged in their disease management. These moderators will positively influence their group members through the role model effect.

A dietitian experienced in counseling will support the moderators if problems arise and they will supervise all moderators once a month via online meetings. During the supervision, the dietitian will reflect on the past month and discuss the next steps of the IMS strategy with the moderators. If necessary, the communication expert can provide further assistance during these meetings.

Furthermore, we expect an additional positive social effect: participants will identify with their *mattermost* group and, in the next step, with the DiabPeerS trial. Hence, they will be interested in a successful intervention and participate actively. Also, frequent personal contact between the central study staff (EH, MH, AEZ) and the participants throughout the whole trial (initial appointment, four measurements, supervision meetings) will support adherence [50].

The IMS strategy (see {11a}), the core element of this trial, aims to improve diabetes self-management. Taking into consideration that regular medical appointments and monitoring are central in diabetes self-management, we assume that this increasing competence will support adherence to intervention as well.

Additionally, clinical visits will be designed as conveniently for the participants as possible [50, 51]. The participants will have easy access to the locations of training sessions and measurements: they can choose one out of four central locations in Lower Austria for their measurements. These locations are well known and easily accessible: the St. Pölten University of Applied Sciences and hospitals in Wr. Neustadt, Hollabrunn, and Mauer/Amstetten. These locations are equally distributed over Lower Austria from a geographical point of view and can be reached comfortably by car as well as public transport. The training sessions for the participants will take place after the first measurement at the same location. The training sessions for the moderators will be held at the St. Pölten University of Applied Sciences. Therefore, only individuals from St. Pölten or the surrounding areas are eligible to become moderators. If a participant misses one measurement, it is possible to make a new appointment within a certain timeframe.

Furthermore, study staff will call participants to schedule visits and send them reminders via SMS and e-mail 48 h before the appointment. During each measurement, participants and moderators will have the opportunity to discuss their results, such as body composition, with an experienced dietitian, which is not very common in Austria and will increase engagement [50].

Additionally, participants and moderators will receive a financial compensation of 50 EUR and a small gift after the last measurement.

### Relevant concomitant care permitted or prohibited during the trial {11d}

All participants should proceed with their standard therapy [4], and the moderators should continue to participate in the disease management program “Therapie aktiv – Diabetes im Griff” (https://www.therapie-aktiv.at) [52] during the trial.

It is also possible for participants to subscribe to the disease management program “Therapie aktiv – Diabetes im Griff” during the trial. This program was launched in Austria in 2007 and aims to organize long-term and high-quality care for patients with type 2 diabetes mellitus. It is voluntary and free of charge for physicians as well as for patients. It implements evidence-based clinical guidelines and supports patient empowerment, regular medical examinations, and lifestyle advice [52]. At the end of 2020, 14,976 patients with type 2 diabetes mellitus and 296 doctors in Lower Austria - or 93,099 patients with type 2 diabetes mellitus and 1917 doctors at the national level - participated in this disease management program according to internal data of the Austrian Health Insurance Fund.

### Provisions for post-trial care {30}

Trial participation entails only minimal risk compared to standard therapy alone, which will be continued after the trial. Therefore, no special provisions for post-trial care are included.

### Outcomes {12}

Data will be collected four times over a period of 14 months: at baseline (T0), 3 months after the start of the intervention (T1; T0+ 3 months), at the end of the intervention (T2; T0+ 7 months), and after the follow-up (T3; T0+ 14 months), including the following collection of biochemical, psychosocial, and behavioral parameters during all four data collection points.

The primary outcome is the level of HbA_1c_ [%] measured using TOSOH G8 (Sysmex Austria GmbH).

Secondary outcomes are:

Psychosocial parameters:
Social support will be measured using the “Fragebogen zur Sozialen Unterstützung” (F-SozU) [53]: the F-SozU operationalizes social support as perceived or anticipated support from the social environment. The short form consists of the following subscales: “emotional support,” “practical support,” “social integration,” “stress from the social network.” The F-SozU involves of 14 items using a five-point Likert scale with the endpoints “1”(does not apply) and “5”(accurate).Self-efficacy will be measured using the “General Self-Efficacy Scale” (GSE) [54]: the GES consists of ten items designed on a four-point Likert scale with the endpoints “1” (not at all true) and “4” (exactly true) and assesses optimistic self-beliefs to cope with several challenges in life.Depression will be measured using the “Patient Health Questionnaire-9” (PHQ-9) [55]: the PHQ-9 asks for all nine criteria of depression as defined in the Diagnostic and Statistical Manual of Mental Disorders (DSM-IV) using a four-point Likert scale with the endpoints “0” (not at all) and “3”(nearly every day).Diabetes distress will be measured using the “Diabetes Distress Scale” (DDS) [56]: the DDS includes for dimensions of distress (“emotional burden,” “regimen distress,” “interpersonal distress,” “physician distress”). The DDS consists of 17 items using a six-point Likert scale with the endpoints “1” (not a problem) and “5” (a very serious problem).Quality of life will be measured using the “Short-Form-Health Survey” (SF-12) [57]: the SF-12 includes eight dimensions (“physical functioning,” “role limitations due to physical problems,” “bodily pain,” “vitality,” “general health perceptions,” “social functioning,” “role limitations due to emotional problems,” “mental health”). The summary scores “physical component summary” and “mental component summary” (0–100 scales) can be calculated from the specified scales.Diabetes knowledge will be measured using the “Diabetes Knowledge Test” (DKT) [58] with forward and retranslation: the DKT consists of 20 statements about diabetes which have to be rated as “true,” “false,” or “don’t know.” Based on the answers, a difficulty index (percent of patients who scored correctly) is calculated.

Behavioral parameters**:**
Medication adherence will be measured using the “A14-scale” [59]: the A14 consists of 14 items of non-adherent behaviors phrased in a non-threatening and non-judgemental way using a five-item Likert scale with the endpoints “4” (never) to “0” (very often).Dietary behavior and alcohol consumption will be measured using a food frequency questionnaire (FFQ), which assess “dietary behavior” and “alcohol intake” during the past 4 weeks with 53 items and the endpoints “never” and “more than 4 times a day”.Physical activity will be measured using the “International Physical Activity Questionnaire Short Form” (IPAQ-SF) [60, 61]: the IPAQ-SF asks seven questions to assess “vigorous-intensity” and “moderate-intensity” physical activity as well as “walking” and “sitting.” Participants indicate the time in minutes or hours for each activity level. Based on this information, three levels of physical activity (low, moderate, high) are calculated and expressed in metabolic equivalent of task (MET) minutes per week.Diabetes self-management behaviors will be measured using the “Summary of Diabetes Self-Care Activities German” (SDSCA-G) [62]: the SDSCA-G focuses on the past 7 days related to the diabetes self-care activities “nutrition,” “physical activities,” “blood glucose testing,” “foot care,” and “smoking.” The SDSCA-G consists of 11 items and participants mark the number of days the mentioned behavior was performed on an eight-point Likert scale with the endpoints “0” (0 days) to “7” (7 days). While the first ten items are calculated to a score and four sub scores (diet, exercise, blood-glucose testing, foot care), the eleventh item focuses on smoking habits.Clinic and communication visits (health professional visits in the past 6 months, hospital stays in the past 6 months).

Biochemical parameters:
Fasting blood glucose [mg/dl] as measured using Cobas 8000 (Roche Austria GmbH)Total cholesterol [mg/dl] as measured using Cobas 8000 (Roche Austria GmbH)High-density lipoprotein (HDL) [mg/dl] as measured using Cobas 8000 (Roche Austria GmbH)Low-density lipoprotein (LDL) [mg/dl] and triglycerides [mg/dl] as measured using Cobas 8000 (Roche Austria GmbH)Blood pressure [mmHg] as measured using Boso Medicus uno OABody height [cm], body weight [kg] and body fat [%] as measured using Seca mBCA 555. The device measures body weight with a scale, body height with ultrasound length measurement and body composition by the voltage drop of the alternating current in one step.Waist circumference [cm] to calculate the waist-to-height ratio as measured using an ergonomic, step less, and extendible measuring tape

Additionally, demographic data and personality traits will be surveyed in the baseline assessment (T0). Demographic data include age, gender, education, living arrangement (marital status), income, employment status, immigration background [63], and clinical information (age at diagnosis, on insulin, other medical therapies, list of prescribed medications). Personal traits will be assessed using the Big Five Inventory German (BFI-2) [64]. The BFI-2 captures “extraversion,” “agreeableness,” “conscientiousness,” “negative emotionality,” and “openness,” each represented by three sub-facets. The BFI-2 consists of 60 items using a five-item Likert scale with the endpoints “1” (strongly disagree) to “5” (strongly agree).

Additionally, participation in the disease management program “Therapie aktiv – Diabetes im Griff” as well as pregnancy and illicit drug use / non-medical use of prescription drugs will be evaluated at each measurement.

Communication data (real-time):

As part of the data export solution of the IMS communication data, an export script is provided in which individual rooms - these correspond to the groups assigned for the experiment - are listed. Such communication protocols containing the communication data of the individual groups can be retrieved on a daily basis. These data include, for example, the persons who have sent a post, sent texts and files, timestamps, or quotes. This information will be used to quantify the IMS communication activities.

The posts will be evaluated by content analysis to explain and interpret the results of (H2) diabetes self-management behaviors, (H3) quality of life of participants, and (H4) medication adherence of participants. The codebook will be developed in collaboration with medical professionals for the coding of adherence and non-adherence behaviors. The quantified data will then be made available for the in-depth analysis of questionnaire data and medical scores.

According to past research [65–67], personality traits such as extraversion can influence our communication behavior: extraverted individuals speak more often, make more eye contact, smile, and nod more frequently than introverted persons. (H5) Therefore, we assume that extraversion will correlate positively with the number of posts as well as the number of reactions and emojis to posts from others.

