### Sample size {14}

An a priori calculation was performed using G-Power [68] for the primary outcome variable HbA_1c_, using an ANCOVA at 5% level of significance and 80% power. Based on previous research, we assumed a small to medium effect size for group differences in HbA_1c_ means (partial eta squared = 0.05, which corresponds to an effect size *f* = 0.229) [69–71]. Considering a 30% dropout ratio, we will include 98 randomly assigned participants in each group (196 total). The intervention group will be subdivided into seven IMS groups made up of 14 participants and one moderator each. Therefore, nine moderators (seven plus two for the compensation of possible drop-outs) will be additionally recruited (205 persons in total, 196 participants plus nine moderators). Although the moderators will participate in the assessments, their data will not be included in the analyses.

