## Statistical methods

### Statistical methods for primary and secondary outcomes {20a}

Data will be analyzed using IBM SPSS Statistics 26 or greater (IMB Corporation, Armonk, NY, USA). The significance level will be set at 5%. Generally, metric data will be checked for normal distribution using a histogram of each variable, as well as for skewness and kurtosis. To illustrate descriptive parameters, the arithmetic mean and the 95% confidence interval will be stated for metric data. Interval variables or nominal scaled variables will be shown as frequencies. Repeated measures ANCOVA will be used to compare the control and intervention groups concerning primary and secondary outcome parameters. Non-normal metric data will be analyzed using the Mann-Whitney *U* test, the Kruskal-Wallis signed rank test, or the Friedman-Test [73].

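### HbA1c is measured at four visits, but no visit or model term is named to decide H1, so the stated 80% power is not established for the planned repeated measures ANCOVA

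*Protocol article*

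**What the plan says.** All places are in the protocol article.

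- Outcomes {12}: "Data will be collected four times over a period of 14 months", at baseline (T0), 3 months (T1), 7 months (T2, end of the intervention) and 14 months (T3, end of follow-up). The endpoint is then given as "The primary outcome is the level of HbA_1c_ [%] measured using TOSOH G8 (Sysmex Austria GmbH"), with no visit, change or contrast.
- Objectives {7}: H1 says that the intervention lowers HbA1c compared with standard therapy. It names no visit either.
- Sample size {14}: the calculation was done "using an ANCOVA at 5% level of significance and 80% power". On the effect, the section says "we assumed a small to medium effect size for group differences in HbA_1c_ means". It puts that effect at a partial eta squared of 0.05, or f = 0.229. There is no visit, repeated factor, number of measurements or within-patient correlation. The result is "Considering a 30% dropout ratio, we will include 98 randomly assigned participants in each group (196 total").
- Statistical methods {20a}: "Repeated measures ANCOVA will be used to compare the control and intervention groups" on primary and secondary outcomes alike. The covariate and the deciding term are not named.

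**The concern.** The visits answer different questions. T2 closes the seven months of guided support. T3 follows seven further months in which the group runs without professional guidance (Trial design {8}, Intervention description {11a}). T2 therefore measures the effect of the guided intervention and T3 measures maintenance. Objectives {7} speaks to both, so a reader cannot tell which one H1 is about.

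The repeated measures model does not settle this. Its group effect averages over visits, and its interaction asks whether the arms diverge over time. A contrast at one visit is a third option. Each can give a different answer from the same data. A positive H1 could be challenged as picked afterwards, and a negative one as a real T2 effect averaged away.

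The time point of the primary outcome defines the claim. It belongs in the protocol and is not detail that is normally left to an analysis plan.

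**Working it through.** **1. Reproducing the stated sample size.** Inputs from Sample size {14}: partial eta squared 0.05, alpha 5%, power 80%, dropout 30%. Two arms come from Trial design {8}: "The participants will be randomized at a ratio of 1:1".

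- f = sqrt(0.05/0.95) = 0.229. With equal arms, d = 2f = 0.458.
- Noncentral F with 1 numerator df, denominator df N - 3 (two groups, one covariate), lambda = N x f². At N = 152, lambda = 152 x 0.0524 = 7.97 and power is 80.1%. N = 151 gives 79.8%. Using 0 to 3 covariates does not change the 152.
- 152 x 1.3 = 198, within two of the stated 196, which is also 2 arms x 7 groups x 14. Dividing instead, 152/0.7 gives 218, which does not match.
- At the same f, 2 or 3 numerator df would need 187 or 212 evaluable before any dropout. A one-sided test needs 120 (156 or 172 after inflation). None of these matches.

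The figure is therefore that of a 1-df test. A multi-df interaction was not what was powered.

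**2. Power of the terms that the planned model offers.** Assumptions, none of them in the protocol: compound symmetry with between-visit correlation r = 0.6 or 0.7, 152 evaluable, and a T2 effect set so that a T2 ANCOVA adjusted for T0 has f = 0.229 (80% power). There are three patterns over T1-T2-T3: half-full-half, half-full-nil and constant. Below, m is the vector of arm differences by visit, m̄ is its mean, and N/4 = 38.

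- *T0 as a repeated level.* In raw SD units the full effect is 0.458 x sqrt(1 - r²) = 0.366 (r = 0.6) or 0.327 (r = 0.7), and zero at T0. Group effect: lambda = 38 m̄² / [(1 + 3r)/4], 1 df. Interaction: lambda = 38 Σ(m - m̄)² / (1 - r), 3 df.
- *T0 as covariate.* The residual correlation is r' = r/(1 + r) = 0.375 or 0.412, and the full effect is 0.458 residual SDs. Group effect: lambda = 38 m̄² / [(1 + 2r')/3], 1 df. Interaction: lambda = 38 Σ(m - m̄)² / (1 - r'), 2 df.

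Example, half-full-half at r = 0.6:

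- T0 as level: m̄ = 2 x 0.366/4 = 0.183, lambda = 38 x 0.0335/0.70 = 1.82, power 27%.
- T0 as covariate: m̄ = 2 x 0.458/3 = 0.305, lambda = 38 x 0.0932/0.583 = 6.07, power 69%.

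Power at r = 0.6 / 0.7:

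| Pattern | Group effect, T0 level | Interaction, T0 level (3 df) | Group effect, T0 covariate | Interaction, T0 covariate (2 df) |
|---|---|---|---|---|
| half-full-half | 27 / 21% | 54 / 57% | 69 / 67% | 24 / 25% |
| half-full-nil | 17 / 14% | 69 / 72% | 45 / 44% | 61 / 64% |
| constant | 52 / 40% | 74 / 77% | 96 / 95% | 5 / 5% |

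**3. Type I error if any visit may decide.** For three post-baseline tests at two-sided 5%, simulation with 400,000 draws gives the chance of at least one false positive as about 12.5%, 11.8%, 10.9% and 9.8% for correlations of 0.5, 0.6, 0.7 and 0.8 between the tests.

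**4. Power of a single-visit ANCOVA at the planned size.** 196 x 0.7 = 137 evaluable. Lambda = 137 x 0.0524 = 7.18, power 75.8%.

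**The case against.** The strongest counter-argument is that the group effect of a repeated measures ANCOVA is itself a 1-df test of a difference in HbA1c means, which is how Sample size {14} describes what was powered. If the partial eta squared of 0.05 refers to that effect, 152 evaluable and 80% follow unchanged. With T0 as covariate, the natural reading of an ANCOVA, and an effect that is constant from T1, power is about 95%. This stands. A reader might infer that the 80% belongs to a test that the plan does not run, but the documents do not support that. They show only that the figure is not tied to a stated visit or term.

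Two further points also stand. The low group-effect figures (14-52%) hold only if T0 enters as a level of the repeated factor. The 10-12% type I error needs separate visit tests with the best one chosen. Statistical methods {20a} plans one model and no such selection, so the figure shows what the open wording would permit, not what is planned.

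It can also be said that the deciding term is analysis-plan detail, and that the two figures in Participant timeline {13} are not shown. The choice of term alone might be left to an analysis plan. The primary time point should not be, because H1 has no definite meaning without it. A flow diagram or visit schedule would not normally name the deciding test.

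**Conclusion.** The point holds in a limited form. The protocol fixes neither the visit nor the model term that decides H1, and the stated 80% is therefore not established for the planned analysis. It does not follow that the 80% is false for every reading of that analysis.

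Within what the wording allows, power runs from 14% to 96% for the group effect and from 5% to 77% for the interaction, depending on the role of T0 and on how the effect changes over visits. These ranges rest on assumed correlations of 0.6 to 0.7, compound symmetry, 152 evaluable patients and the three effect patterns. The absence of a primary visit rests on the text alone.

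Naming a visit does not by itself restore 80%. Under the plan's own dropout, the matching single-visit ANCOVA has about 76%.

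**What to change.** In Outcomes {12} and Statistical methods {20a}, name one primary visit. State that H1 is decided by a single between-arm ANCOVA of HbA1c at that visit, with T0 HbA1c as covariate, at two-sided 5%. This matches the 1-df test that the sample size reproduces, and it needs no new model class.

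T2 is the natural choice if the question is the effect of the guided intervention. If maintenance is the main question, which the stated aim of lasting improvement would also support, the sponsor should name T3. Report the other visits and the repeated measures model as secondary.

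In Sample size {14}, state the power for that contrast: about 76% with 137 evaluable of 196 randomised. Holding 80% under 30% dropout would need 218 randomised.

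Cost: no change to visits or procedures, and none to patient numbers if 76% is accepted. It does need a protocol amendment with ethics committee and funder approval and then a registry update (section {25}), and the printed power figure becomes slightly less favourable. The change should be made before post-baseline HbA1c is seen by arm. The protocol version is dated November 2021 and the first intervention starts in April 2022, so that was possible when this version was written.
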